## Abstract

**Background:**

Non-suicidal self-injury (NSSI) is a growing healthcare problem. Individuals with NSSI have an increased risk of suicidality. Due to stigma, they may self-injure in secret, which means they might not seek help until events have escalated to include suicidal ideation or a mental disorder. Interventions delivered via mobile phone applications (apps) have been linked to reductions in self-injury. This protocol outlines a trial, which examines whether the Zero Self-Harm intervention, consisting of an app for people with NSSI, can reduce the number of NSSI episodes, suicide ideation, and depressive symptoms.

**Methods:**

The trial will be conducted as a 6-month 2-arm, parallel-group, multicentre, pragmatic, randomized clinical superiority trial. The intervention group will receive the app and instructions on how to use it, while the control group will be allocated to a waitlist and allowed to download the app after 6 months. After inclusion, participants will be asked to complete questionnaires at baseline, 3 months, and 6 months. The primary outcome is the number of NSSI episodes during the preceding month, as measured at the 6 months follow-up with the Deliberate Self-Harm Inventory. A total of 280 participants, 140 in each arm, will be included.

**Discussion:**

This trial will assess the effectiveness of the Zero Self-Harm intervention to reduce the number of NSSI episodes. If effective, the app will have the potential to support a large group of people with NSSI. Considering the stigma related to NSSI, the fact that the app may be used in private and anonymously might make it an appealing and acceptable option for support. The app was developed in collaboration with people with lived experiences related to current and/or previous NSSI. As a result of this, the app focuses on minimizing harm, rather than stopping NSSI. This might enhance its utilization.

**Trial registration:**

ClinicalTrials.gov NCT04463654. Registered on 7 June 2020.

**Supplementary Information:**

The online version contains supplementary material available at 10.1186/s13063-024-07932-1.

## Background

Non-suicidal self-injury (NSSI) is defined in the fifth version of the Statistical and Diagnostic Manual of Mental Disorders (DSM-5) as “the deliberate, self-inflicted destruction of body tissue without suicidal intent and for purposes not socially sanctioned, includes behaviours such as cutting, burning, biting and scratching skin” [1]. Though difficult to determine, the overall prevalence of NSSI among adolescents, young adults, and adults is estimated to be 17%, 13.4%, and 5.5%, respectively, reported in meta-analyses [2, 3]. NSSI is characterized by an early onset; in a US sample, about 27% of participants reported that self-injurious behaviour was initiated around the age of 15–16 years, while 38.6% of participants commenced at the age of 17–24 years [4].

People with NSSI have higher risks of dying, in particular by suicide, when compared to the general population [5–7]. NSSI is, furthermore, associated with a range of mental health problems, such as anxiety, depression, eating disorders, and drug and alcohol abuse [8–11]. The most common method of NSSI is cutting, while other behaviours include scratching, head banging, breaking bones, and burning oneself [12]. The majority of people use more than one method. Using a range of methods and several episodes of self-injury behaviour are considered markers of severe NSSI [13]. NSSI can be an addictive behaviour; approximately half of the adolescents with NSSI have had multiple episodes of self-injury [14, 15]. NSSI is often hidden due to stigma and shame [11, 16, 17].

Individuals with high levels of impulsivity can act rashly when experiencing negative emotions and, in this respect, NSSI may serve as a coping strategy and provide a form of immediate relief [18]. This supposition is supported by the fact that individuals with NSSI report greater difficulties with emotion regulation [19, 20] and have high levels of emotion dysregulation [21].

It is estimated that only 1 in 8 persons present at hospital or seek help in the public health sector after NSSI [14, 15]. People with NSSI might not be considered in need of specialized treatment, implying that, when left untreated, the behaviour might escalate to a point where the person becomes suicidal or develops a mental illness [5, 6].

In addition to being low-cost, easily delivered, and scalable, self-help mobile phone applications (apps) for people with NSSI have shown promising findings in randomized controlled trials, including moderate reductions in self-reported self-cutting and self-injurious episodes; symptoms of depression and anxiety; and improvements in coping with unpleasant emotions and thoughts [22]. Still, evaluations conducted in different settings are warranted to determine the true effectiveness of apps in reducing NSSI [23].

Findings from qualitative studies suggest that the option of receiving immediate support at home and in an anonymous format enhances the acceptability of the app [22–24]. Features, such as daily mood tracking, have been seen as a way to improve emotional self-awareness [25]. In addition, self-help apps may support individuals with different severity levels of NSSI [26, 27].

The goal of the Zero Self-Harm (ZSH) intervention is to motivate people with NSSI to reduce their self-injurious behaviour rather than to completely stop it, which for many might seem unrealistic and deter them from using the app. The ZSH app is developed from the MyPlan app, which was developed in 2012 and whose effect is currently being investigated for its ability to reduce suicide ideation [28, 29]. MyPlan has been reviewed by users and clinical staff with promising qualitative feedback [30, 31].

The objective of this trial is to investigate whether adults with NSSI who receive the ZSH app have fewer NSSI episodes at 6-month follow-up when compared to adults with NSSI who do not receive the ZSH app in a randomized clinical superiority trial. We hypothesize that the ZSH app can help reduce the number of NSSI episodes by enhancing coping skills to better manage impulsive urges. Further, working with the app might reduce emotional dysregulation and trait impulsivity, which are core features of NSSI, and thereby lower associated symptoms, such as suicide ideation and depression.

## Methods and design

The trial will be conducted as a 2-arm, parallel-group, multicentre, pragmatic, randomized clinical superiority trial. A total of 280 participants, 140 in each arm, will be included from clinical and non-clinical settings in Denmark and followed over 18 months (see Fig. 1). The intervention group will receive the ZSH app, while the control group will be allocated to a waitlist condition. The recruitment of participants was initiated in October 2020. See Table 1 for the entries to the World Health Organization Trial Registration Data Set.

**Fig. 1 Fig1:**
[figure not shown]
Flow diagram of the Zero Self-Harm intervention

**Table 1 Tab1:** World Health Organization Trial Registration Data set

Data category	Information
Primary registry and trial identifying number	ClinicalTrials.gov NCT04463654
Date of registration in primary registry	07/07/2020
Secondary identifying number	Trygfonden 127390, The Regional Ethics Committee in the Capital Region of Denmark H 19024725
Source(s) of monetary or material support	TrygFonden reference number: 127390
Primary sponsor	[name], Psychiatric Centre North Zealand; Denmark
Contact for public queries	KA: [contact]
Contacts for scientific queries	KA: [contact]
Public title	Zero Self-Harm - a Mobile Phone Application to Reduce Non-suicidal Self-injury
Scientific title	Zero Self-Harm - a Mobile Phone Application to Reduce Non-suicidal Self-injury: A Randomized Clinical Superiority Trial
Country of recruitment	Denmark
Health condition(s) or problem(s) studied	Self-injurious behavior
Intervention(s)	Device: Zero Self-Harm app, safety plan app for smartphones
Key inclusion and exclusion criteria	Ages eligible for study: ≥ 18 years; sexes eligible for study: both Inclusion Criteria: Engagement in two or more episodes of NSSI in the past month, have a smartphone (IPhone or Android phone), fluent in Danish, skills sufficient to enable use of the Zero Self-Harm app, provide an informed written consent. Exclusion Criteria: Lack of informed consent, further planned specialized treatment focused on NSSI.
Study type	Allocation: Randomized Interventional Model: Parallel Assignment Masking: Single (Outcomes Assessor) Primary Purpose: Prevention
Date of first enrolment	October 15, 2020
Target sample size	280
Recruitment status	Not recruiting
Primary outcome(s)	Number of self-harm episodes: Deliberate Self Harm Inventory [Time Frame: 6 months]
Key secondary outcome(s)	Suicide ideation: Becks Suicide Ideation Scale [Time Frame: 6 months] Depression: Major Depression Inventory (MDI) [Time Frame: 6 months] Well-being: WHO Well-being Index [Time Frame: 6 months] Self-esteem: Rosenberg's Self-Esteem scale [Time Frame: 6 months]

### Recruitment

We will strive to include individuals with a wide range of NSSI, from those with shorter duration and milder symptoms who might not be in contact with mental healthcare facilities to those with more severe and chronic NSSI who are already attending treatment at Danish mental health facilities. Non-profit organizations, such as Danish Mental Health Fund (Psykiatrifonden), The Danish National Association for Eating Disorders and Self-harm (Foreningen Spiseforstyrrelser og selvskade), and the Danish telephone helpline for people with suicide thoughts (Livslinien), as well as municipal service centres, educational institutions for individuals aged ≥18 years, psychiatric inpatient units and outpatient clinics, and psychiatric and general emergency departments will be contacted with regard to the referral of potential participants. Furthermore, the trial will be announced through non-profit organizations’ websites and social media platforms and presented at educational institutions for individuals ≥ 18 years old. The research assistant responsible for recruitment will routinely visit relevant locations, such as in-patient clinics in the Capital Region of Denmark, and give reminders to participating venues through e-mails and phone calls.

### Criteria for inclusion and exclusion

Individuals who fulfil the following criteria are included: (1) have had two or more physical NSSI episodes within the past month, (2) own a smartphone (iPhone or Android), (3) are fluent in Danish, (4) are able to install and use the ZSH app, (5) provide informed written consent, and (6) are ≥18 years old. Individuals who (1) are attending specialized treatment for NSSI (Dialectical Behavioral Therapy), e.g. at newly established outpatient clinics in the Capital Region of Denmark, or (2) are currently being involuntarily treated will not be enrolled.

### Enrollment and randomization

Interested individuals will be encouraged to contact the research assistant through phone or e-mail. They will be provided with verbal and written information about the study, in which it is emphasized that participation is voluntary and that they may withdraw their consent at any time. They may take time to consider or discuss the participation with a next of kin before deciding whether to enrol in the study. During the enrollment phase, the potential participants will be interviewed by using the Mini-International Neuropsychiatric Interview (MINI) [32] and informed consent will be collected via an e-mail from REDCap [33] to the secure digital platform e-Boks where Danish citizens receive verified information [34]. The research assistant will make sure to get the informed consent in the enrollment phase. The participant information materials and informed consent form are available from the corresponding author.

After enrollment, participants will be administered the baseline questionnaires. Subsequently, they will be randomly assigned to either the intervention or the control group in a 1:1 allocation, using REDCap’s feature for a computer-generated sequence randomization. The randomization will be stratified by sex and number of NSSI episodes, as measured at baseline by the Deliberate Self Harm Inventory, to avoid overrepresentation of participants with a high number of NSSI episodes in one group. This stratification will be also facilitated through REDCap. The research assistant will generate the allocation sequence in REDCap after enrolling the participant and inform the participant which group, they are assigned to.

As part of the enrollment process, all participants will be informed that they can contact the research assistant in case of questions or technical problems. Participants will also receive information on where they can seek help if needed, for instance through helplines and the emergency services, such as 1318 and 112.

### Intervention

Participants allocated to the intervention group will receive the ZSH app. The app was adapted to the target group through focus-group interviews with people with lived experiences related to NSSI. Based on their suggestions, the app consists of following elements: (1) a tool for listing warning signs of self-injurious thoughts; (2) a tool to identifying coping strategies when self-injurious thoughts arise, including a list of suggestions formed by users; (3) a daily mood tracking option, including pop-up reminders; (4) a place to write down dreams and how to realize them; (5) a place for collecting pictures, music, YouTube videos, which can cheer one up, and write positive message for oneself to practise a positive self-image; (6) a place to reflect on previous NSSI-episodes and read stories from other users; (7) direct phone links to emergency services and nearest map directions for emergency departments. The app is listed under an undisclosed name in Google Play and Apple Store to avoid that people not included in the project will find the ZSH app and start using it.

As part of active onboarding measures to the ZSH app, participants will receive an e-mail instructing them how to download the ZSH app from Google Play or Apple Store. Once an account has been set up, a pop-up message will invite the participant to watch instruction videos explaining to them how to use the app. Participants in the intervention group are also invited to a phone call 1 week after inclusion by the research assistant for providing further information on how to use the ZSH app and to encourage the participants to use the app. Throughout the trial, the research assistant will be available to answer questions regarding the ZSH app and give technical support.

Participants allocated to the waitlist control group will be invited to download the ZSH app once answers to the last questionnaire have been submitted after 6 months.

### Outcomes

The primary outcome, the number of NSSI episodes during the preceding month, will be measured using the validated 17-item Deliberate Self Harm Inventory (DSHI) [35] at the 6-month follow-up (see Fig. 2). This measure includes questions on a number of NSSI episodes for 17 frequently used methods, e.g. cutting, burning, and scratching. As the original inventory uses a recall period of 4 months, a modified version adapted to 1 month will be used. This modification was done to limit any recall bias regarding the number of NSSI episodes [36]. The DSHI questionnaire will be administered at baseline and 3- and 6-month follow-up.

**Fig. 2 Fig2:**
[figure not shown]
SPIRIT overview of enrollment and data collection

Explorative outcomes include suicide ideation, depressive symptoms, quality of life, and self-esteem. Suicide ideation will be measured by the Becks Suicide Ideation Scale (BSS), a 21-item self-report questionnaire measuring suicidal ideation [37]. Depressive symptoms will be measured using the Major Depression Inventory (MDI) [38], a short questionnaire consisting of 12 items capturing depressive symptoms. It can be scored as a diagnostic tool, but also used as a measure of severity as the sum of the item scores [38]. Quality of life will be measured by the WHO Wellbeing Index (WHO-5), a widely used brief questionnaire to measure subjective psychological wellbeing, consisting of 5 questions [39, 40]. Self-esteem will be measured by Rosenberg’s Self-Esteem Scale (RSE), which consists of 10 items measured on a Likert scale [41]. All explorative outcomes will be administered at baseline and 3- and 6-month follow-up.

User satisfaction will be measured by a modified Client Satisfaction Questionnaire (CSQ-8) at 3-month follow-up among participants allocated to the intervention group. An overview of the assessments and timepoints in the trial is provided in the SPIRIT figure (see Fig. 2). See Additional file 1 for the SPIRIT checklist [42].

### Safety measure

To assess potential harmful effects, the 20 first participants who receive the ZSH app will be contacted after completing the 3-month questionnaire for an interview regarding their experiences. The interviewed participants will be asked systematically if they had any negative experiences using the app. If any adverse effect (AEs) or serious adverse effects (SAEs) in relation to the use of the self-help app occurs, it will be reported to the Trial Steering Committee and it will be decided which action will be made, either minor changes to prevent other future events or to stop the trial.

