## Discussion

Emerging research suggests that specialized apps targeting self-injurious behaviour, which can be used anonymously and in private, have the potential to help people with NSSI [23, 24]. However, randomized controlled trials confirming the effectiveness of these apps in different settings are warranted [23, 24].

The ZSH intervention has several strengths. First, by involving stakeholders and people with lived experiences in the development of the app, the app’s content is likely to be relevant to the target group. Second, by having a focus on minimizing harm, the app might be more appealing and acceptable to a broader group of users. Third, by listing the app under an undisclosed name, contamination of the trial’s data will be limited.

Potential limitations should be noted. Firstly, although the app was developed in collaboration with individuals with lived experiences, it may not address the needs of everyone engaging in NSSI. Individuals with NSSI are characterized by broad age spans, diagnoses, severity and versatility of NSSI, and co-morbidities. Although it might be beneficial to also collect feedback and insights from next of kin and professionals, this was beyond the scope of this intervention.

Secondly, it is important to acknowledge that the use of the app might maintain or possibly worsen NSSI. To investigate this potential limitation, the first 20 participants will be asked after 3 months about whether they have had any negative experiences or side effects of the app. Other potential limitations could be linked to how users learn how to use the app, which for some participants can be difficult and overwhelming. It might result in some participants using the app only a few times or not at all. Even though a thorough onboarding process is carried out, more continuous and structured support might improve the usage of the app. Another way of combining a more structured support with technology could also have been by using for instance automatically collected smartphone sensor data, which is not included in this trial. In general, having a self-help app as an intervention can be challenging since technological development is an on-going process. Some of the app features designed to be user-friendly can potentially become outdated during the trial. Once the trial is started, the app cannot undergo significant changes, and this could limit the possibility of continuously ensuring the relevance of the app and its design.

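### The one dedicated harm check is an uncontrolled interview of 20 app users, and the two-arm DSHI and BSS data are given no stated safety use

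*Protocol article*

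**What the plan says.** The Safety measure section sets out one dedicated procedure for detecting harm: "the 20 first participants who receive the ZSH app will be contacted after completing the 3-month questionnaire for an interview regarding their experiences". On content it says: "The interviewed participants will be asked systematically if they had any negative experiences using the app". The same section adds a reporting route: if an adverse or serious adverse effect "in relation to the use of the self-help app occurs, it will be reported to the Trial Steering Committee", which then decides on action. That route is not confined to the 20, but the article does not say how events outside the 20 are found, or whether they are sought in controls.

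The Discussion states the worry: "it is important to acknowledge that the use of the app might maintain or possibly worsen NSSI". It then names the tool: "To investigate this potential limitation, the first 20 participants will be asked after 3 months".

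The Outcomes section describes data that bear on the same worry without restriction to one arm. The DSHI episode count is the primary outcome at 6 months, and "The DSHI questionnaire will be administered at baseline and 3- and 6-month follow-up". For suicide ideation (BSS) and the other scales: "All explorative outcomes will be administered at baseline and 3- and 6-month follow-up". The Statistical analysis section compares the 6-month episode count between arms by intention to treat, with two-tailed tests and confidence intervals. Neither the Safety measure section nor the Discussion links these data to the question of harm.

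**The concern.** The protocol asks whether the app makes self-injury worse and assigns that question to a method poorly suited to it.

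- **No comparator.** The Discussion accepts that a participant's condition may deteriorate during the trial. Interviews in one arm cannot tell deterioration caused by the app from deterioration that would have happened anyway.
- **Selection.** As the Safety measure section is worded, the interview follows completion of the 3-month questionnaire. An early app user who got worse and stopped answering would not be reached. The Discussion itself expects avoidance and dropout.
- **Size.** Twenty interviews can miss harms that affect several per cent of users.

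What is at stake is the weight given to a reassuring safety statement. If the interviews turn up nothing and the worsening question is answered from them, the conclusion rests on very little, although randomised data on self-injury and suicide ideation lie in the same database.

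**Working it through.** **Inputs from the article.** 20 interviews (Safety measure); 140 per arm, difference 3.5 episodes, SD 9, power 90%, type I error 0.05 (Sample size); two-tailed tests (Statistical analysis). The significance threshold is printed as 0.5 in Statistical analysis; the calculations here use the 0.05 of the Sample size section.

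**Assumptions.** The article gives no rate of harm or of worsening. All event rates, subgroup sizes and loss rates below are assumed for illustration.

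1. **Reproduce the plan's sample size.** n per arm = 2 × (1.960 + 1.282)² × 9² / 3.5² = 139 by the normal approximation. The t-test version gives 139.92, rounded up to 140. The stated 140 reproduces, with power 90.2%.

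2. **What the primary comparison can say about mean worsening.** The SE of the difference is 9 × √(2/140) = 1.08, so the 95% CI half-width is 1.96 × 1.08 = 2.1 episodes. Because the test is two-sided, power is the same in either direction: about 90% for a mean worsening of 3.5 episodes. With assumed losses of 10%, 20%, 30% or 40%, power is 87%, 83%, 78% or 71%.

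3. **What the interviews can say.** They cover 20/140 = 14% of the app arm. With no report in 20, the one-sided 95% upper limit is 1 − 0.05^(1/20) = 13.9% (two-sided limit: 1 − 0.025^(1/20) = 16.8%). If only 14 of the 20 were interviewed (assumed), it is 1 − 0.05^(1/14) = 19.3%. The chance of seeing no case at all in 20 is (1 − p)^20:
   - p = 1%: 82%
   - p = 2%: 67%
   - p = 5%: 36%
   - p = 10%: 12%

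4. **What a mean difference can hide.** Suppose 10% of app users worsen by 10 episodes and the rest are unaffected. The mean shift is 0.10 × 10 = 1 episode. Then 1/1.08 = 0.93, and power is about P(Z > 1.96 − 0.93) = 15%.

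5. **What a by-arm table could add.** With 140 per arm, power for a 10-point excess in the proportion worsening is 80%, 65% or 49% at assumed control proportions of 5%, 10% or 20%. If both arms had 20%, the 95% CI half-width for the difference would be 1.96 × √(2 × 0.20 × 0.80/140) = 9.4 points. So the table is informative but not decisive, which is why it should be descriptive.

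**The case against.** A reader might infer that harm is assessed solely through the 20 interviews, and that the trial therefore cannot answer its own question. The documents do not support that. More self-injury is simply the adverse direction of the primary outcome, which is compared between randomised arms with a two-tailed test (step 2). Suicide ideation and depressive symptoms are also measured without restriction to one arm. The adverse-effect route covers more than the 20, and the Data collection section provides for regular steering committee review and possible review by the ethics committee and independent data monitoring. This stands, and it limits the point.

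It can also be said that the interviews are an early look at the first users and were never meant to estimate a rate. The reference to the completed questionnaire may be timing rather than a condition, since the Discussion omits it, and non-responders are contacted by the research assistant. That is fair for the Safety measure section read alone. It does not cover the Discussion, which presents the interviews, and nothing else, as the means of investigating worsening.

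Finally, a condensed article may leave safety tables and the detail of adverse-event collection to the full protocol or analysis plan. For that reason, missing detail is not the point here. The point is the method that the article itself names. The objection that any rise in a one-month count is a crude and noisy measure is correct, and it is met by using the proportions only beside the planned comparison of means.

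**Conclusion.** The concern holds in limited form. The only dedicated harm assessment is small and uncontrolled, and the Discussion relies on it for the worsening question. No reports in 20 would leave a true rate of up to 13.9% open, and a harm affecting an assumed 5% of users would go wholly unseen with probability 36%. The interviews cannot attribute any deterioration to the app.

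The trial is not blind to worsening: at full follow-up and SD 9, the primary comparison has about 90% power for a mean worsening of 3.5 episodes. What remains uncovered is worsening in a minority (about 15% power in the assumed example), together with any stated safety use of the 3-month DSHI or of the BSS. Two limits apply to every between-arm comparison here: outcomes are unblinded self-reports, and the Data collection section has the data of participants who discontinue deleted, which could remove some who got worse. This is a worthwhile, inexpensive improvement and does not invalidate the design.

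**What to change.** - Keep the interviews and describe them as an early qualitative check.
- Before the A/B-coded analysis described under Blinding begins, pre-specify a descriptive safety table by randomised arm at 3 and 6 months. It should give the proportion with more NSSI episodes on the DSHI than at baseline and the proportion with a higher BSS score than at baseline, with 95% CIs for each between-arm difference and the number missing per arm.
- Revise the Discussion so that the worsening question rests on this comparison as well as on the interviews.

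**Cost.** One extra exploratory table from scales already in the questionnaires. Dichotomising loses some information, which is acceptable because the table supplements the planned comparison of means.

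A new questionnaire item on negative experiences, or going back to early non-responders, is not recommended. Recruitment ran from October 2020 to September 2023, and the last 6-month questionnaire is dated 22 February 2024 (Trial status). A new item would reach only the last participants, and early users would be asked about events long past.

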### Data collection

The participants will be administered questionnaires at baseline (*T*_0_) and at two follow-up time point (*T*_1_=3 months and *T*_2_= 6 months). At baseline, the participants will undergo the MINI interview and there will be socio-demographic questions, including age, gender, and use of psychiatric services. The MINI is administered by the research assistant. All other questions will be self-administered and sent to the participant by e-mail at baseline and follow-up. All the participants will be allocated an individual trial identification number and all data will be collected in REDCap in a central computer storage under Mental Health Services in the Capital Region of Denmark.

To promote participant retention, robot-generated reminders will be sent out 1 week after the dissemination of questionnaires. If participants have not completed the questionnaire a week after the reminder was sent out, the research assistant will contact the participant and encourage them to answer the questionnaires and assist with any technical problems. All the participants will receive a minor gift card to a coffee shop once the questionnaire is completed. If a participant wishes to discontinue their participation, their data will be deleted. Still, the number of discontinuations will be reported in the Consort flow diagram. The Project Management Group is planned to meet on a weekly basis and the Trial Steering Committee will meet approximately every third month to review trial conduct and progress. The Ethical Committee and the independent Data Monitoring can review trial conduct throughout the whole trial period.

To secure data confidentiality, data on participants will be stored in a logged and closed computer drive in the Mental Health Services in Capital Region of Denmark. It will be stored until 5 years after the trial has finished. Afterwards, data will be permanently deleted.

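### The safety clause ties escalation and the stop decision to app-related events, so serious events are filtered by attribution and have no control-arm counterpart

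*Protocol article*

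**What the plan says.** The Safety measure section provides for one interview, after the 3-month questionnaire, with the first 20 people who receive the app, asking about negative experiences with it. It then sets the escalation rule: an adverse or serious adverse effect that arises "in relation to the use of the self-help app occurs, it will be reported to the Trial Steering Committee", which then chooses between minor changes and stopping the trial. No other section states a stop decision.

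Under Intervention, waitlist participants "will be invited to download the ZSH app once answers to the last questionnaire have been submitted after 6 months".

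Data collection describes the wider oversight: "the Trial Steering Committee will meet approximately every third month to review trial conduct and progress", and the Ethical Committee and independent Data Monitoring may review conduct at any time. No event listing and no stopping rule is attached to either. The same section says: "If a participant wishes to discontinue their participation, their data will be deleted". Only the number of discontinuations is kept for the flow diagram.

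On outcomes: "The DSHI questionnaire will be administered at baseline and 3- and 6-month follow-up", and for suicide ideation, depressive symptoms, well-being and self-esteem, "All explorative outcomes will be administered at baseline and 3- and 6-month follow-up". Neither sentence is limited to one arm.

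**The concern.** The Background states the underlying risk plainly: "People with NSSI have higher risks of dying, in particular by suicide, when compared to the general population". Serious events are therefore to be expected in both arms, and the Discussion accepts that the app could maintain or worsen NSSI. In such a population a suicide attempt by an app user can look like the ordinary course of the illness. A rule that asks first whether an event relates to the app puts a case-by-case judgement where a randomized comparison could stand. It also leaves the Trial Steering Committee, under this clause, with events from one arm and no background rate to read them against.

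At stake is the committee's ability to interpret serious events, and how the trial report presents them. The primary NSSI comparison is hardly affected.

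**Working it through.** **1. Who can trigger the rule.** The Sample size section plans 140 per arm, 280 in total. Control participants have no app before their last questionnaire, so the share who cannot produce a qualifying event during follow-up is 140/280 = 50%.

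**2. What is already compared between arms.** Inputs from Sample size: difference 3.5 episodes, SD 9, power 90%, type I error 0.05. Two-tailed testing is from Statistical analysis.
- Reproducing the plan's figure: n per arm = 2 × (1.960 + 1.282)² × 9² / 3.5² = 139 by the normal approximation. The t-based version gives 139.9, so 140, as stated.
- Standard error of the difference = 9 × √(2/140) = 1.076. A harm as large as the planned benefit is 3.5/1.076 = 3.25 standard errors, and power = Φ(3.25 − 1.96) = 0.90. This assumes complete data.

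A mean worsening of NSSI of that size would therefore be seen at the end. Suicide ideation (BSS) and depression (MDI) scores are also available at 3 and 6 months.

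**3. What those measures leave out.** The Background defines NSSI as "the deliberate, self-inflicted destruction of body tissue without suicidal intent", so suicide attempts lie outside the primary count. The Outcomes section describes the DSHI as a count of episodes by method, not of episodes that needed hospital care. BSS and MDI are scale scores. No section describes tabulating attempts, admissions or deaths by arm, and no escalation is tied to any scale.

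**4. Why a one-arm count is hard to read.** The article gives no serious-event rate, so assume a 6-month risk without the app of 5%, 10% or 20%. Suppose 14 events are seen among the 140 app users.

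| Assumed risk without app | Expected in 140 | Ratio for 14 observed |
|---|---|---|
| 5% | 7 | 14/7 = 2.0 |
| 10% | 14 | 14/14 = 1.0 |
| 20% | 28 | 14/28 = 0.5 |

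The same 14 events could mean a doubling, no change or a halving.

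**5. What a comparator would add.** With 21/140 against 14/140 (illustrative), the risk ratio is 1.5. SE(log RR) = √(1/21 − 1/140 + 1/14 − 1/140) = 0.324, giving a 95% CI of 0.80 to 2.83. For 80% power at two-sided 5%, the app-arm risk would have to reach 15.0%, 22.3% or 34.9% against 5%, 10% or 20%, which are ratios of about 3.0, 2.2 and 1.7. A by-arm table would therefore be descriptive only.

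**6. How events would come to light.** After baseline, the stated data are self-administered questionnaires sent by e-mail, and none is described as asking about attempts or admissions. The 1-week call and the interview of the first 20 are for the app arm only. Events that become known would therefore be found more readily in that arm.

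**The case against.** The strongest reply has four parts.

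- **The clause is an instruction, not an exclusion.** It says what happens when app-related effects occur. It does not say that other events go unreported, and the phrase sets no explicit causality test. This is fair, and it softens the attribution point. It does not remove the comparator point: even if every event during app use counted, no control-arm event could qualify.
- **Other oversight exists, and the article is a condensation.** The committee's regular meetings and the Data Monitoring may look at serious events, and the full protocol may collect them in both arms. This stands as a limit. The oversight text, however, attaches no event listing or stop decision, and the escalation clause is a stated rule rather than an omitted detail.
- **The named hazard is already compared by arm.** This stands. A reader might infer that worsening NSSI would go unnoticed. The documents do not support that, since DSHI, BSS and MDI are collected at both follow-ups without arm restriction.
- **A table of known events would be unequally ascertained.** This stands too. A reader might expect the rewording to give an unbiased account of serious events by arm. It cannot, without equal active collection in both arms.

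A reader might also count the deletion of leavers' data as evidence of bias in the primary mean. That is a separate missing-data question and adds nothing here. Deletion matters to this point only because a serious event in someone who later leaves may not reach the report.

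**Conclusion.** The point holds in a limited form and is worth correcting. As written, the clause makes committee reporting, and the article's only stop decision, depend on a link to the app. Half of those randomized cannot meet that condition during follow-up, and app-arm serious events judged to be the usual course of the condition need not be escalated.

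The gap is confined to discrete serious events, such as suicide attempts and admissions. Its size cannot be stated from the documents, because every serious-event risk used above is an assumption. Even complete two-arm collection would detect only large ratios. The conclusion rests on the wording of the article. It does not establish that the trial lacks any other safety route, or that the primary result is biased. Recruitment ran until September 2023 and the last questionnaire was due to go out on 22 February 2024, so escalation during follow-up is largely past and the remaining value lies in the trial report.

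**What to change.** Reword the clause along these lines: *Every serious adverse event that becomes known in either arm, whether or not thought related to the app, is reported to the Trial Steering Committee and the independent Data Monitoring; relatedness is recorded separately.*

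In the trial report, add a descriptive by-arm table with:
- deterioration from baseline on DSHI and BSS at 3 and 6 months, with the definition fixed before the data are opened;
- all known serious events, including suicide attempts and hospital-treated self-harm, whatever the attribution;
- for participants who discontinue, an anonymous by-arm count of serious events already known, where the consent terms allow.

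Prepare the table under the A/B coding in the Blinding section. Add relatedness only after unmasking, since it would reveal the arms. No interim harm boundary is proposed.

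The cost is one clause, one table and slightly more reporting work, with no new visit or questionnaire. The serious-event rows must carry the caveat that the app arm has more staff contact and so more chance of events being noticed. The DSHI and BSS rows are the comparable ones.
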